### Implementation Phase

Implementation of the device as the new standard of care for monitoring will be executed in 2 distinct phases to ensure a thorough evaluation and implementation of this monitoring system (Table 1).

During phase 1 (the initial phase; months 1-3), patients will continue to receive the current standard of care, which involves manual spot checks and MEWS measurements by nursing staff. Concurrently, all health care staff will receive training on the application, data interpretation, and protocol adherence concerning the solution to optimize the infrastructure before its implementation.

Following phase 1 (in month 4; the evaluation and validation period), the preimplementation phase will be evaluated. Predictive accuracy will be evaluated by comparing device data against clinical outcomes such as complications, intensive care unit transfers, or MEWS-triggered interventions using area under the receiver operating characteristic curve analysis.

In phase 2 (months 5-8), the wearable will become the primary tool for patient monitoring, supplemented by manual spot checks by nurses as needed. This phase aims to evaluate the integration into standard care.

During the whole study, every minute data are securely stored. During phase 2 of the study, 6 times a day, median values of the previous 4-hour window will be uploaded to the EHR. In case of signal loss or low-quality readings, the system generates flags, allowing for assessment of signal-to-noise ratio (SNR).

**Table 1 table1:** Psychometric properties and statistical analysis.

Objective	Instrument	Variable	Statistical test	Achievement criteria
Fidelity	SUS^a^	Continuous	Unpaired *t* test or Mann-Whitney *U* test	Fidelity achieved when protocol adherence is ≥95%
Acceptance	SC^b^/day	Continuous	Descriptive statistics	Acceptance achieved when ≥75% of nurses use the device regularly
Acceptance	SC/patient	Continuous	Descriptive statistics	Acceptance achieved when ≥75% of nurses use the device regularly
Acceptance	IWS^c^	Ordinal	1-way ANOVA	Acceptance achieved when ≥75% of nurses use the device regularly
Adoption	EBPAS^d^	Continuous	Repeated measures ANOVA	Adoption achieved when device use exceeds 70% by clinical staff
Appropriateness	SNR^e^	Continuous	Descriptive statistics	Adoption achieved when device use exceeds 70% by clinical staff
Appropriateness	ADE^f^	Continuous	Descriptive statistics	Appropriateness achieved with minimal ADEs

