### Outcomes

The primary objective of this study is to evaluate the implementation of a new wearable on the surgical ward at Catharina Hospital Eindhoven. This will be achieved by assessing its usability, degree of implementation, and the workload for nursing staff. The primary outcome will be acceptability, specifically evaluating workload as measured by the Integrated Workload Scale (IWS). The IWS is a comprehensive tool that provides multidimensional descriptions and gradations of workload, ranging from “not demanding” to “work too demanding” on a 9-point Likert scale. This scale is suitable for both periodic assessment and real-time monitoring of tasks, with measurements conducted throughout the entire study period.

For secondary outcomes, the study will apply the framework of the taxonomy of implementation outcomes of Proctor et al [12], focusing on adoption, feasibility, appropriateness, predictive accuracy, and technical feasibility. Adoption will be measured by the Evidence-Based Practice Attitude Scale and the System Usability Scale, along with the amount of spot checks conducted in addition to the standard monitoring.

Feasibility will be evaluated by determining the extent to which health care employees can successfully implement the device, and by measuring the time required to perform and process manual spot checks or digital monitoring checks. Appropriateness will be assessed by examining the SNR and counting the number of (suspected) adverse events that occur during or result from the use of the wearable.

Additionally, the predictive accuracy for early detection of health deterioration and postoperative complications among patients will be evaluated through focus group discussions. Technical feasibility will involve analyzing the availability of data on the web platform, including monitoring time and the types and quantities of algorithm artifacts, such as low-quality data during the monitoring of photoplethysmography values.

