Approximately 70 nurses from the surgical ward will participate in the study and complete the IWS. In addition, 10 nurses and 5 physicians will voluntarily join focus groups to conduct an in-depth evaluation of the new implementation. These focus groups, which will be established prior to the study’s commencement, will meet 3 times during the study period to discuss the progress of the study and share their experiences with the implementation. A structured analysis of fidelity, feasibility, and acceptability will be conducted by the focus group, and this information will be processed and objectified using a thematic analysis devised by Braun and Clarke [11].

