## Results

Staff training was completed in October 2024, and full implementation is ongoing. Up to 150 participants intend to be enrolled in the study. Preliminary findings, including data on usability and workload, are expected by July 2025 (see details in Table 2).

**Table 2 table2:** Measurement timetable for psychometric properties.

Objective	Instrument	0^a^	1	2	3	4 (evaluation/validation)	5	6	7	8 (evaluation/validation)
Fidelity	SUS^b^						Q^c^			Q
Acceptance	SC^d^/day				AD^e^					AD
Acceptance	SC/patient				AD					AD
Acceptance	IWS^f^	Q			Q		Q	Q	Q	Q
Adoption	EBPAS^g^	Q			Q				Q	Q
Appropriateness	SNR^h^									AD
Appropriateness	ADE^i^									AD
Feasibility	Thematic analysis				FG^j^			FG		FG
Time efficiency	Time measurement		M^k^	M	M		M	M	M	M
Predictive accuracy	MEWS^l^ and CREWS^m^		M	M	M	AD and M	AD (and M)	AD (and M)	AD	AD

^a^Numbers 0-8 represent the study months, starting from baseline (month 0) through to month 8.

^b^SUS: System Usability Scale.

^c^Q: questionnaire.

^d^SC: spot check.

^e^AD: administered data.

^f^IWS: Integrated Workload Scale.

^g^EBPAS: Evidence Based Practice Attitude Scale.

^h^SNR: signal-to-noise ratio.

^i^ADE: adverse device event.

^j^FG: focus group.

^k^M: manual measurement.

^l^MEWS: Modified Early Warning Score.

^m^CREWS: Continuous Remote Early Warning Score.

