## Discussion

This study is expected to demonstrate that the implementation of continuous vital sign monitoring using the viQtor wearable device is feasible within a surgical ward setting. We anticipate that this technology will be perceived as acceptable and usable by health care professionals, and that its integration may contribute to a measurable reduction in perceived nursing workload. Importantly, by including continuous SpO₂ monitoring, the system may offer added clinical value in identifying early signs of postoperative deterioration.

While earlier studies have assessed the technical accuracy of wearable monitoring devices, relatively few have focused on their integration into clinical workflows. For instance, Breteler et al [8] validated a similar system in high-risk surgical patients, but implementation outcomes such as usability or staff adoption were not the focus. Bellomo et al [7] also examined automated advisory systems, but their routine use in general hospital wards remains uncommon.

Our study distinguishes itself by applying a structured implementation framework, specifically the revised Medical Research Council guidance [10] and the taxonomy of implementation outcomes of Proctor et al [12]. This approach allows us to assess whether the device not only works but also can be realistically adopted in daily practice.

A notable addition in our protocol is the continuous monitoring of SpO₂, a parameter that was lacking in earlier studies such as those involving a Healthdot device. Since respiratory complications are among the more frequent and severe postoperative issues, continuous SpO₂ tracking may enhance the early recognition of patient decline [4,6,13].

The study’s multidisciplinary design, combining clinical, technical, and implementation expertise could be seen as a strength. The use of validated instruments—including the IWS [14], Evidence-Based Practice Attitude Scale [12], and the System Usability Scale—ensures a structured and multidimensional evaluation.

Limitations of this study can be expected as well. As a single-center trial focusing on patients undergoing elective surgery, its findings may not be directly generalizable to other hospital departments or to emergency or critical care populations. Additionally, while the viQtor device captures data at regular intervals, data loss or reduced signal quality could occur. These technical aspects will be explored through SNR analysis and artifact tracking.

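### The 1-way ANOVA assigned to the primary workload scale, if run over its six survey waves, does not test wearable months against manual months

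*Protocol article*

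**What the plan says.** The Outcomes section makes workload primary: "The primary outcome will be acceptability, specifically evaluating workload as measured by the Integrated Workload Scale (IWS". Table 1 (Implementation Phase section) then assigns the test: "IWS^c^ Ordinal 1-way ANOVA". It names no factor, levels or comparison. The achievement criterion in the same row is "Acceptance achieved when ≥75% of nurses use the device regularly", which concerns device use and is not a difference in IWS.

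Table 2 shows six IWS questionnaires, "Acceptance IWS^f^ Q Q Q Q Q Q", under months 0, 3, 5, 6, 7 and 8.

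The design sets a manual period against a wearable period: "During phase 1 (the initial phase; months 1-3), patients will continue to receive the current standard of care", then "In phase 2 (months 5-8), the wearable will become the primary tool for patient monitoring". The respondents are given as "Approximately 70 nurses from the surgical ward will participate in the study and complete the IWS". The Discussion hopes that "its integration may contribute to a measurable reduction in perceived nursing workload".

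The Statistical Analysis section lists tests in general terms. It allows linear mixed models or repeated measures ANOVA for repeated measures, but does not tie either to the IWS.

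**The concern.** The study's question about workload is a comparison of two phases with an expected direction. A 1-way ANOVA over six waves asks whether any wave mean differs from any other. It can therefore be significant because of movement inside one phase, or even between the two waves before the device is in use, and its result has no sign. Someone would then have to decide, with the data in view, which waves carry the headline.

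The test also spends five degrees of freedom on a question that needs one, and it treats repeated ratings by the same nurses as independent. A real, steady reduction could be missed. This matters because the IWS is the primary outcome and Table 1 gives it only this test.

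**Working it through.** **Inputs from the article.** About 70 nurses (Outcomes); six waves, of which months 0 and 3 precede device use and months 5, 6, 7 and 8 fall in phase 2 (Table 2); 1-way ANOVA (Table 1). The article gives no alpha, SD, effect size or power for the IWS, so there is no stated figure to reproduce.

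**Assumptions.** Two-sided alpha 0.05; SD 1 (effects in SD units); normal scores; the same 70 nurses at every wave with complete data; equal within-nurse correlation r of 0.2, 0.5 or 0.8.

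**Is wave the factor?** Table 1 gives the SUS, measured twice, a two-sample test. The EBPAS, measured four times, and the IWS, measured six times, get ANOVAs. That pattern points to wave but does not prove it.

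**Tests compared**
- 1-way ANOVA, F on 5 and 6 x 69 = 414 df.
- Repeated-measures omnibus F, on 5 and 5 x 69 = 345 df.
- Phase contrast within nurse: mean of months 5-8 minus mean of months 0 and 3, t on 69 df.

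The contrast weights are -1/2 (twice) and +1/4 (four times), and their squares sum to 0.50 + 0.25 = 0.75. Hence SE = sqrt((1 - r) x 0.75 / 70) = 0.0926, 0.0732 and 0.0463 at r = 0.2, 0.5 and 0.8.

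**Rejection when the phase means are equal** (simulation)

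| Pattern (months 0, 3, 5, 6, 7, 8; SD units) | 1-way ANOVA | Phase contrast |
|---|---|---|
| 0, 0, +0.40, +0.13, -0.13, -0.40 | 99-100% | 5% |
| -0.25, +0.25, 0, 0, 0, 0 | 32-57% | 5% |

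In the first pattern the sum of squared deviations is 2 x 0.16 + 2 x 0.0178 = 0.356, and 70 x 0.356 = 24.9. In the second it is 2 x 0.0625 = 0.125, and 70 x 0.125 = 8.75. These between-wave signals drive the F test, while the phase contrast is exactly zero.

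**Power for a steady -0.25 SD in months 5-8**

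The grand mean is -1/6. The squared deviations sum to 2 x (1/6)^2 + 4 x (1/12)^2 = 0.0833, and 70 x 0.0833 = 5.83. For the contrast, 0.25/SE = 2.70, 3.42 and 5.40.

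| r | 1-way ANOVA | Repeated-measures omnibus | Phase contrast |
|---|---|---|---|
| 0.2 | 34% | 50% | 76% |
| 0.5 | 22% | 75% | 92% |
| 0.8 | 7% | 100% (rounded) | 100% |

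The step from the first to the second column is the cost of ignoring pairing. The step from the second to the third is the cost of the omnibus form. At correlation 0, where pairing plays no part, the 1-way ANOVA has 42% power and the contrast 67%.

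**How the contrast behaves under a start-up peak.** With only month 5 raised by 0.5 SD, the contrast shifts by 0.5/4 = 0.125 SD. Then 0.125/SE = 1.35, 1.71 and 2.70, and it rejects in 26/39/76% of trials.

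Simulated percentages carry an error of one or two points.

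**The case against.** **The factor is inferred.** The Implementation Phase section describes two phases. If phase with two levels were the factor, the ANOVA would itself be a before-versus-after test, and the objection to an omnibus test would fall. The SUS comparison is only suggestive, because both SUS waves lie in phase 2. This stands as a limit on certainty. It does not remove the need for the article to say which reading is meant.

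**Contrasts and multiplicity rules usually belong in an analysis plan.** That is right, and their absence from a condensed article is not the point here. The point is narrower: the article does name a test, and on its natural reading that test does not fit the question.

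**A reader might infer that free choice among wave comparisons inflates the false-positive rate.** The documents do not support that for the plan as written. If comparisons follow only a significant 1-way ANOVA, and nothing changes at any wave, that test rejects in just 1.7/0.1/0.0% of trials at correlation 0.2/0.5/0.8, because it ignores pairing. The gate gives no protection once some waves truly differ, which is the situation in the patterns above.

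**A time-course test is a defensible first look.** The IWS is collected throughout the study, and the hoped-for reduction is cautious Discussion text, not a formal hypothesis. Both are fair. Neither turns an undirected test into an answer about the two phases. An average over months 5-8 and a settled-use comparison are different targets, and the documents do not choose between them.

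**Conclusion.** The point holds in a limited form. The article assigns its primary outcome a test that, read over six waves, has no direction, can reject almost always when the phase means are equal, and has 34/22/7% power for a steady 0.25 SD reduction, against 76/92/100% for a single within-nurse contrast. Part of that loss comes from ignoring pairing and part from the omnibus form.

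The percentages rest on the assumed SD, alpha, correlation, normal scores and complete repeat ratings by 70 nurses. That the F test lacks direction and does not isolate the phases follows from its form and depends on none of these.

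A reader might also infer that a named contrast would show what the device did. It would not: there is no concurrent control, and before-after confounding remains whichever test is used. Nor does this point make the study invalid. It affects what the headline workload result can mean.

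**What to change.** In Table 1, replace the 1-way ANOVA in the IWS row with one primary contrast: mean IWS over months 5-8 minus mean IWS over months 0 and 3. Estimate it within nurse from the linear mixed model that the Statistical Analysis section already allows, with wave as a categorical factor, and report it with a two-sided 95% CI. Label all other wave comparisons exploratory. If phase was the intended factor, this wording makes that explicit.

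The cost is one table cell and one sentence, with no new data, staff or patients. The downside should be stated: a start-up peak at month 5 also moves this contrast, as shown in the working, so the month-by-month estimates should be reported beside it.

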## Methods

### Setting

This prospective implementation study with retrospective data analysis (the REQUEST [Remote Monitoring by viQtor Upon Implementation on a Surgical Department] trial) will be conducted at a large teaching hospital. All adult patients (aged 18 years and older) admitted to the surgical department for elective procedures will be eligible for inclusion, provided they meet our inclusion criteria and provide informed consent. Patients unable to wear the device or unwilling to participate will be excluded.

The viQtor device, developed by SMARTCARE, was selected due to its proven capability for autonomous, continuous monitoring and its established structure for seamless data transfer into the electronic health record (EHR). The device is CE (Conformité Européenne)-certified and transmits data every minute via a cellular network without the need for any hub. Each vital sign—heart rate, respiratory rate, and peripheral oxygen saturation (SpO₂)—is updated every minute, with data being transferred to the EHR. The device provides median values from the last 4 hours for each vital sign, which means that the system aggregates data over that period to ensure stability in measurements. In the event of missing data, the system generates flags to indicate the absence of readings, and data imputation strategies will be applied. By using clinical-grade photoplethysmography sensor technology, the device allows accurate tracking of heart rate, respiratory rate, and SpO₂. Although the device can also measure skin temperature, this parameter will not be used in this study.
The solution comprises a device with a charger and an armband. The device is worn on the upper arm under clothing and is applied upon admission (Figure 1).

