### Statistical Analysis

Quantitative data will be analyzed using IBM SPSS Statistics (version 26.0). Descriptive statistics will be used to summarize categorical data (frequencies and percentages) and continuous variables (means and SD or medians and IQRs, depending on the distribution). Normality will be assessed using the Shapiro-Wilk test. Group comparisons will be made using *t* tests, ANOVA, Mann-Whitney *U*, or chi-square tests where appropriate. For repeated measures, linear mixed models or repeated measures ANOVA will be used. Qualitative data from focus groups will be coded and thematically analyzed following Braun and Clarke’s [11] approach.

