### Ethical Considerations

This study involves human participants and has been approved by Medical Research Ethics Committees United (reference number W24.065). Written informed consent to participate will be obtained from all participants prior to inclusion in the study.

All data collected will be pseudonymized before analysis to protect participants’ privacy. Personal identifiers will be replaced with unique study codes, and the key linking codes to participant identities will be stored separately in a secure, access-restricted location. Only authorized study personnel will have access to this information.

Participants will not receive any financial compensation or other incentives for participation in this study. Participation is voluntary, and participants may withdraw at any time without any consequences for their care.

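### Table 1 assigns the four-wave EBPAS to repeated measures ANOVA, which in its standard form drops any nurse with a missed wave, although the plan already permits a mixed model that keeps them

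*Protocol article*

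**What the plan says.** In the protocol article, Table 1 (Methods, Implementation Phase) treats the EBPAS as a continuous measure of adoption and gives one test for it: "Repeated measures ANOVA". The cell offers no alternative, whereas the System Usability Scale row names two tests.

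The Statistical Analysis section is broader: "For repeated measures, linear mixed models or repeated measures ANOVA will be used". It gives no rule for choosing between the two. The software is SPSS version 26.

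Table 2 (Results) marks an EBPAS questionnaire in four columns: 0, 3, 7 and 8. Its footnote explains the columns: "Numbers 0-8 represent the study months, starting from baseline (month 0) through to month 8".

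The only count of nurses is in the Outcomes section and refers to the Integrated Workload Scale (IWS): "Approximately 70 nurses from the surgical ward will participate in the study and complete the IWS". No count is given for the EBPAS.

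The one statement on imputation is in the Setting section and concerns device readings: "In the event of missing data, the system generates flags to indicate the absence of readings, and data imputation strategies will be applied". Nothing shown applies it to staff questionnaires.

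**The concern.** Standard repeated measures ANOVA needs a full row of data per person. A nurse who returns three of four EBPAS questionnaires contributes nothing, and the three are thrown away. Incomplete series are foreseeable in a voluntary staff survey that runs for eight months. The Ethical Considerations section states that "participants may withdraw at any time without any consequences for their care", wording that fits patients best but is given for participants generally.

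Two things are at stake. The first is precision, because the analysed group can be much smaller than the group that answered. The second is validity. If a nurse's chance of answering later depends on earlier attitude, the complete cases are a selected group and their mean change need not be the ward's mean change. A likelihood-based mixed model uses all observed waves and remains valid under missing at random, provided it is correctly specified. Of the two methods it permits, the plan has named for this outcome the one that discards more data and needs the stronger assumption.

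**Working it through.** The article states no sample size, power or non-response figure for the EBPAS, so there is no figure of its own to reproduce. The consequence is worked out under stated assumptions.

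**Inputs**
- Waves: 4 (months 0, 3, 7 and 8), from Table 2.
- Nurses: N = 70, from the Outcomes section. This is stated for the IWS; using it for the EBPAS is an assumption.
- Response per wave: q = 95%, 90%, 80% or 70%. Assumed, and independent between waves unless stated otherwise.
- Linkage: within-nurse analysis needs answers linked across waves. Ethical Considerations states that "Personal identifiers will be replaced with unique study codes", which makes this possible.

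**Step 1: nurses and questionnaires kept**

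Complete series = N × q⁴. Nurses with at least one wave = N × (1 − (1 − q)⁴). Share of returned questionnaires discarded = 1 − q⁴/q = 1 − q³.

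| q | q⁴ | Nurses analysed | Nurses lost | With at least one wave | Questionnaires discarded |
|---|---|---|---|---|---|
| 95% | 0.815 | 57 | 13 | 70 | 14% |
| 90% | 0.656 | 46 | 24 | 70 | 27% |
| 80% | 0.410 | 29 | 41 | 70 | 49% |
| 70% | 0.240 | 17 | 53 | 69 | 66% |

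**Step 2: effect of clustered non-response**

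Independence is near the pessimistic end. Suppose instead that response clusters within nurses, with a beta-binomial model and within-nurse correlation c (assumed). With a + b = 1/c − 1 and a = q(a + b), the complete share is the product of (a + k)/(a + b + k) for k = 0 to 3.
- q = 80%, c = 0.3: 0.800 × 0.860 × 0.892 × 0.9125 = 0.56, or 39 of 70.
- q = 80%, c = 0.5: 0.80 × 0.90 × 0.933 × 0.95 = 0.64, or 45 of 70.
- q = 70%, c = 0.5: 0.70 × 0.85 × 0.90 × 0.925 = 0.50, or 35 of 70.

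**Step 3: precision of the month 0 to month 8 change**

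This change is used only to show precision. Assumptions: SD 1, equal correlation ρ of 0.5 or 0.7 between waves, independent non-response unrelated to attitude, 300 simulated missingness patterns per setting. The complete-case standard error (SE) is √(2(1 − ρ)/n), with n the number of complete series. The mixed-model SE comes from generalised least squares on all observed waves with the covariance known. For ρ = 0.5 and q = 80% these are 0.1895 and 0.1381, a ratio of 1.37. With no missing data the SE is √(2 × 0.5/70) = 0.1195.

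Power is two-sided at 0.05 by the normal approximation, at the effect that would have 80% power with no missing waves. That effect is a yardstick, not a figure from the plan.

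| q | SE ratio, complete-case to mixed | Power, complete-case | Power, mixed model |
|---|---|---|---|
| 95% | 1.07 | 71% | 77% |
| 90% | 1.15 | 62% | 74–75% |
| 80% | 1.36–1.37 | 42–43% | 68% |
| 70% | 1.62–1.66 | 27% | 59–60% |

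**Step 4: an illustration of bias**

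Take a true change of zero and ρ = 0.6, and let nurses with lower baseline attitude skip each later wave more often (logit of missing = −1.5 − baseline). This gives 22% missing per later wave and 52% complete series. Among complete cases the mean is 0.453 SD at baseline and 0.270 SD at month 8, a false change of 0.270 − 0.453 = −0.18 SD. The group was selected for high baselines and then regressed towards the mean. By symmetry, if nurses with higher baselines skipped more often, the false change would be +0.18 SD. The mixed model was not fitted here; its consistency under this mechanism is a general property of likelihood methods under missing at random.

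**The case against.** The case against has real weight.

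- **The mixed model is already in the plan.** The Table 1 cell may be a short label in a condensed article, and the full protocol or analysis plan may settle the choice. Listwise deletion is written nowhere; it is a property of the standard procedure, and imputing questionnaires first would avoid it. This stands as a limit. The point is not that a missing-data rule is absent, but that the article names a specific method for this outcome when a better one is already permitted. Nor do the two places contradict each other: Table 1 picks one of the two methods that Statistical Analysis allows.
- **The size is assumed.** This stands. No EBPAS respondent number, non-response rate or turnover figure is given. A reader might infer that most of the sample will be lost. Under independence that needs response below about 84% per wave (0.5 to the power ¼ = 0.84), and clustering lowers the threshold.
- **The direction of bias is unknown.** A reader might infer that the nurses who remain are the most engaged, so the change is inflated. The documents do not support this. Selecting nurses with favourable attitudes raises the level but, as in Step 4, can push the change downward.
- **Little hangs on it.** This stands. The EBPAS is one of several measures of a secondary outcome, and the achievement criterion in its row is device use above 70% by clinical staff. A reader might infer that the adoption verdict is at risk; it does not depend on this test.
- **The mixed model is no cure-all.** If response depends on current, unobserved attitude, it is biased too.

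**Conclusion.** The point holds as a minor improvement to a secondary analysis. For an outcome measured four times, Table 1 names a test that in its standard form uses complete series only, while a method that uses every completed questionnaire is already permitted. Assuming 70 nurses and independent response, the analysed group falls to between 57 and 17 as response per wave goes from 95% to 70%. Clustered non-response makes the loss smaller, and full response makes it zero. Precision is lost whenever waves are missed, and bias in either direction is possible when response depends on earlier attitude. The workload outcome, which is primary, and the stated adoption criterion are not affected.

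**What to change.** In the EBPAS row of Table 1, replace the test with a linear mixed model: month as a categorical fixed effect, nurse as a random effect, all available waves included. Keep both waves that precede phase 2, months 0 and 3, in the model. Under Statistical Analysis, add that the mixed model is the method used for the EBPAS, and that it assumes questionnaires are missing at random given the observed answers. The general sentence on repeated measures can otherwise stay as it is; this point gives no ground for changing it for other outcomes.

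The cost is wording only. The planned software fits mixed models, no additional data or participants are needed, and with complete, balanced data the result is essentially the same as that of repeated measures ANOVA. The change is best made before the EBPAS data are analysed.

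### Table 1 judges the appropriateness/SNR row by staff device use, so the stated verdict on appropriateness does not depend on signal quality

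*Protocol article*

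**What the plan says.** The Outcomes section of the protocol article defines the outcome in these terms: "Appropriateness will be assessed by examining the SNR and counting the number of (suspected) adverse events". Adoption is kept separate: "Adoption will be measured by the Evidence-Based Practice Attitude Scale and the System Usability Scale", together with the number of additional spot checks. SNR is not among the adoption measures.

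Table 1 (Implementation Phase) has two rows under appropriateness, both analysed with descriptive statistics:

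- The SNR row has the criterion "Adoption achieved when device use exceeds 70% by clinical staff". The EBPAS row directly above it, under adoption, has the same words.
- The ADE row has the criterion "Appropriateness achieved with minimal ADEs".

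Signal quality also appears elsewhere. The Implementation Phase section says that signal loss and low-quality readings are flagged so that SNR can be assessed. Under technical feasibility, the Outcomes section covers data availability, monitoring time and the "types and quantities of algorithm artifacts, such as low-quality data". The Discussion accepts that data loss and reduced signal quality may occur and adds: "These technical aspects will be explored through SNR analysis and artifact tracking". Table 2 schedules both SNR and ADE at month 8 only.

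**The concern.** The text names two components of appropriateness, and the table gives a criterion for only one of them. The criterion printed beside SNR measures staff behaviour and declares a different objective achieved. A reader applying Table 1 at month 8 would compute the SNR and then find no rule that uses it.

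This matters because in months 5-8 the wearable is the primary monitoring tool, and the authors themselves expect some signal loss. A populated health record would not settle the question, since the uploaded values are 4-hour medians and the Setting section plans imputation for missing data. SNR is one of the few planned measures aimed directly at whether the device delivered usable readings. If it cannot influence the verdict on appropriateness, a statement that appropriateness was achieved says less than the outcome definition promises. The closing paragraphs of the article say that a successful implementation may support wider deployment.

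**Working it through.** The 70% figure is a fixed decision threshold, not a derived quantity, so there is nothing to reproduce numerically. The check compares the outcome definitions with the criteria.

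**Step 1. Definition against criterion**

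| Source | Component | Criterion | Does signal enter? |
|---|---|---|---|
| Outcomes text | SNR | Part of appropriateness, no threshold | Yes, as a measure |
| Table 1, SNR row | SNR | Staff device use above 70%, labelled adoption | No |
| Table 1, ADE row | ADE | Minimal ADEs, labelled appropriateness, no number | No |

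**Step 2. Could another criterion cover it?** The remaining Table 1 thresholds are protocol adherence of at least 95% (fidelity), at least 75% of nurses using the device regularly (acceptance), 80% of clinicians able to implement it (feasibility), a fall of at least 20% in monitoring time (time efficiency) and AUROC of at least 0.80 (predictive accuracy). None names SNR, usable minutes or data availability. The technical feasibility paragraph and the Discussion describe signal quality without a threshold.

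**Step 3. Is it only a table artefact?** The repeated text could be a merged cell flattened when the table was read. There are three possible readings:

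1. *As printed.* The SNR row is judged by staff use. This contradicts both its own row label and the Outcomes section.
2. *The cell is blank, or merged only by accident.* SNR has no criterion. The only appropriateness criterion is about ADEs.
3. *The ADE criterion was meant to cover both appropriateness rows.* It still refers only to ADEs.

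Under all three, the stated appropriateness criterion has no signal term.

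**Step 4. What the rule responds to.** Take staff use of 71% and an ADE count that the authors accept as minimal (both illustrative). With 5% of minutes flagged, the SNR row's criterion is met and the ADE criterion is met. With 95% flagged and the same use and ADE count, both are still met. With staff use at 70% or below, the SNR row's criterion is not met, even if every minute is valid. The 5% and 95% are illustrative and do not come from the article. They show only that, with the other inputs held fixed, the rule does not respond to signal quality.

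**The case against.** The strongest reply has three parts.

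**The cell may be a typesetting or extraction slip.** The acceptance rows also repeat one criterion, so a merged cell is plausible. What would then remain is a missing threshold for a descriptive secondary measure, which a condensed article may leave to a fuller document. This stands in part: a deliberate rule that judges signal by staff use cannot be assumed. But the acceptance rows share one objective, whereas here the text crosses from adoption to appropriateness. The article also does print a criterion for appropriateness, and that criterion omits a component which the Outcomes section includes. The table and the text therefore need reconciling on any reading.

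**The consequence is limited.** A reader might infer that the study never looks at whether the device delivered vital signs. The article does not support that: SNR, data availability, monitoring time and artifacts are all to be described, and unusable data could lower the AUROC that is judged against 0.80.

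**The outcome is not certain.** A reader might also infer that a device with mostly unusable readings is bound to be declared appropriate. That does not follow. Read literally, meeting the SNR row's criterion declares adoption, not appropriateness. Device use, minimal ADEs and ADE itself are not defined in the article. Staff may use a poorly performing device less, particularly as manual spot checks remain available. No probability can be attached to the verdict.

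**Conclusion.** The point holds as a misassigned criterion. Table 1 contradicts the Outcomes section on how SNR is judged, and the only criterion labelled as appropriateness has no signal term. As written, the achievement verdict for appropriateness does not depend on signal quality except indirectly, through whatever effect poor signal has on staff use or on what counts as an ADE.

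The size is one of two declared components of one secondary outcome. It does not touch the primary workload outcome, nor the descriptive reporting of signal quality. The stronger claim, that the whole study could succeed without examining the signal, is not supported.

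The conclusion assumes that the Table 1 criteria are the rules by which achievement will be declared. It does not depend on whether the SNR cell is a real entry, a merged cell or a blank. The point should be corrected before the month 8 analysis.

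**What to change.** - Keep the rule of more than 70% device use on the adoption (EBPAS) row only.
- Give the SNR row a criterion computed from data the study already stores, for example a minimum share of worn minutes, or of scheduled 4-hour windows, with unflagged valid readings. If windows are used, state what makes a window valid.
- Set and justify the minimum value before the month 8 analysis. The article gives no basis for a particular figure, so the choice belongs to the authors.
- State that appropriateness is declared only when both the signal criterion and the ADE criterion are met.

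The edit is one table cell and a sentence of analysis wording, with no new data collection. The real cost is justifying a threshold that the article does not supply, and accepting that appropriateness can then fail on signal quality.
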